### Cardiovascular and Exercise Assessments

Participants will be screened according to Exercise and Sports Science Australia’s Adult Pre-Exercise Screening Tool, and will only be permitted to participate if they are deemed to be of low risk. They will have no known cardiovascular disease, and to the best of their knowledge, be able to perform the exercise task. Participants will be familiarized will all testing procedures. Participants will complete the following battery of tests at baseline (Week 0) and Week 12.

### 24-h Radial Blood Pressure

Participants will be fitted with a BPro wristwatch at their baseline visit (Day 0) and final visit (Day 90) and will be required to wear this for 24 h. The radial artery position will be located and BPro fitted accordingly. The device will be calibrated by measuring the participant’s blood pressure using an automatic sphygmomanometer and appropriately sized cuff three times at the time of fitting the BPro, and the average of these three measurements will be entered into the wristwatch. The BPro may need to be secured in place for some participants using plasters and an “anchor” device. This will only be done if comfortable for the participant.

The BPro captures blood pressure over 24 h at the wrist, eliminating the possibility of a “white coat” effect and providing more reliable blood pressure estimates. It is convenient to use, light weight, non-invasive, non-disruptive, cuffless, and takes a BP reading every 15 min over 24 h. The design of the watch provides a constant force of applanation on the radial artery, thereby capturing the waveforms of the radial artery. The device measures systolic and diastolic blood pressure, heart rate, central aortic systolic pressure (CASP) and 24 h blood pressure patterns. Where there are less than 45 recordings available during a 24 h period the data will be excluded from analysis.

### Six Minute Walk Test

The 6 MWT is a submaximal exercise test that entails measurement of distance walked over a span of 6 min. The 6-min walk distance (6 MWD) provides a measure for integrated global response of multiple cardiopulmonary and musculoskeletal systems involved in exercise. The 6 MWT will be performed in accordance with the published guidelines by the American Thoracic Society (ATS). The test has been marked at 3-m intervals so that an accurate measurement of the walking distance can be performed. Chairs are available at 30-m intervals in case the patients become so symptomatic that they have to stop and sit. Participants will rest comfortably for 10 min prior to the test. During this time blood pressure and heart rate should be measured and potential contraindications assessed. Prior to the test commencing, the participant will stand up and rate his/her dyspnea and fatigue. The Borg scale (Rating of Perceived Exertion) will be used for this. The participant will begin the test with the supervisor/researcher using standardized phrases and an even tone for encouragement at the completion of each minute of the test. The participant will be allowed to rest during the test, but the clock will continue. If the participant cannot continue walking, the test will be stopped and the distance covered recorded. At the conclusion of the test, the participant will be asked to rate his/her dyspnea and fatigue levels and the reason for stopping the test.

### Statistical Analysis

The primary analysis will involve an intention-to-treat (ITT) examination of the effects of treatment (CoQ_10_ Ubiquinol vs. placebo) on CogTrack index scores (attentional intensity index, sustained attention index, working memory capacity index, episodic memory capacity index, and speed of retrieval index) at 90-days compared to baseline. Repeated measures analysis of variance (ANOVA) will be used to examine treatment and study visit × treatment interaction effects, using a subject-specific random intercept term, treatment group as a between-group factor (CoQ_10_, placebo) and study visit as a repeated within-group factor (baseline, 90-days). Pearson’s *r* correlations will be used to explore the relationships between demographic variables (i.e., age, weight, height, education, gender) and CogTrack composite scores, and in the case of significant associations (*p* < 0.05), demographic variables will be included as covariates in the analysis.

Similar statistical techniques will be used to investigate the effects of treatment on secondary outcomes, as well as the CogTrack composite scores at 30- and 60-day time points. Results will be presented as effect sizes using 95% confidence intervals. Overall compliance to treatment will be analyzed by counting each participants remaining supplements at the completion of the trial.

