### Participants

A total of 128 healthy elderly participants (52 per group) aged 60+ years will be randomized. The sample size was selected on the basis of power analysis with G*Power 3.1.9.2, which revealed that with two treatment groups and two primary time points and specifying a significance level of *p* < 0.05, there is an 80% chance of detecting a small-medium effect size (cohen’s *f* = 0.14) for the time × treatment group interaction. Inclusion criteria will include being male or female aged 60 years or older, fluent in written and spoken English, normal or corrected-to-normal eyesight and good general health on the basis of medical history. Exclusion criteria will include being a current smoker, or having a history of the following medical conditions: diabetes, epilepsy, PD, dementia, stroke (or other neurological conditions), traumatic brain injury, current anxiety, depression, alcohol or substance dependence, endocrine, gastrointestinal or bleeding disorder, and uncontrolled hypertension (as determined by a systolic blood pressure >160 mm Hg or diastolic blood pressure >90 mm Hg). Participants will also be excluded if they are currently using over-the-counter herbal or nutritional supplements with known effects on cognition and mood, anti-coagulant drugs, anti-depressants (e.g., selective-serotonin reuptake inhibitors) or anxiolytics (e.g., benzodiazepines).

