### Primary Outcome

The primary study outcome is the effect of CoQ_10_ (Ubiquinol) supplementation on cognitive performance at 90-days, using the composite measures from the CogTrack battery (Wesnes et al., 2017a,b, 2018; Watson et al., 2018). CogTrack is a well-validated and highly sensitive online computerized battery for assessing cognitive function across domains of attention, concentration and vigilance, working memory and executive control, and episodic/declarative memory. Scores from the individual CogTrack tests are used to calculate five index scores: attentional intensity index, sustained attention index, working memory capacity index, episodic memory capacity index, and speed of retrieval index.

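### Five unranked CogTrack indices are all primary, but the trial is sized for a single interaction test at an undivided 0.05; the decision rule and the power basis do not match

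*Protocol article*

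**What the plan says.** The Primary Outcome section defines the outcome at 90 days "using the composite measures from the CogTrack battery", in the plural, and adds: "Scores from the individual CogTrack tests are used to calculate five index scores". None of the five is ranked above the others.

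The Statistical Analysis section carries all five into the primary analysis, an intention-to-treat examination of the effects of treatment "on CogTrack index scores (attentional intensity index, sustained attention index, working memory capacity index, episodic memory capacity index, and speed of retrieval index". Repeated measures ANOVA "will be used to examine treatment and study visit × treatment interaction effects". On reporting it says: "Results will be presented as effect sizes using 95% confidence intervals". The only p < 0.05 in that section is the rule for choosing demographic covariates.

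The Participants section gives the power calculation, "with two treatment groups and two primary time points and specifying a significance level of" p < 0.05. On that basis "there is an 80% chance of detecting a small-medium effect size", namely Cohen's f = 0.14 for the time-by-treatment interaction. This is one test of one variable, and alpha is not divided.

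The Aims and Hypotheses section states one efficacy hypothesis, that cognitive function improves. It calls the cardiovascular, oxidative stress, liver and mood analyses exploratory. The CogTrack analysis is therefore the confirmatory one.

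**The concern.** Five variables serve one efficacy claim, but the error level and the power belong to one test. If a significant result on any one index may be read as support for the hypothesis, the claim no longer has the error rate that a 0.05 level suggests. If some other rule is meant (all five must succeed, alpha is split, or one index leads), the stated 80% power does not describe that rule, or the text that makes all five primary is wrong. At stake is how to read a trial in which one or two of the five indices reach significance, which is a likely pattern.

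**Working it through.** **Inputs from the protocol article.** Five indices (Primary Outcome; Statistical Analysis). Alpha 0.05, 80% power, f = 0.14, two groups, two time points, interaction test (Participants). 52 per group, i.e. 104 in total; the same sentence also gives a total of 128, so both are carried.

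**Assumptions, not in the document.** The correlation rho between an index at baseline and at Day 90, and the correlation r among the five indices (taken as equal for all pairs). Ranges are shown for both.

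**1. Reproducing the sample size.** For the within-between interaction with m = 2 time points, the noncentrality is λ = f² · N · m / (1 − rho), with 1 and N − 2 degrees of freedom. At rho = 0.5 and N = 104, λ = 0.0196 × 104 × 2 / 0.5 = 8.15, and power at 0.05 is 80.7%. N = 102 gives just under 80%, so 104 (52 per group) is reproduced. N = 128 gives 88.2%. The stated power is thus that of one interaction test on one variable at the full 0.05.

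**2. Familywise error over five interaction tests, each at 0.05.**
- Independent indices: 1 − 0.95⁵ = 22.6%.
- Correlated indices: 1 − ∫ φ(x) · p(x)⁵ dx, where p(x) = Φ((1.96 − √r·x)/√(1 − r)) − Φ((−1.96 − √r·x)/√(1 − r)).
- In favour of Ubiquinol only: the same formula without the second term of p(x). At r = 0 this is 1 − 0.975⁵ = 11.9%.

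| Assumed r | At least one false significant index, either direction | At least one falsely favouring Ubiquinol |
|---|---|---|
| 0 | 22.6% | 11.9% |
| 0.3 | 20.9% | 10.5% |
| 0.5 | 18.3% | 9.1% |
| 0.7 | 14.8% | 7.4% |
| 0.8 | 12.7% | 6.4% |
| 0.9 | 10.2% | 5.1% |
| One test only | 5% | 2.5% |

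Simulating the two-arm, two-visit design under the null (52 per arm, 20,000 trials per setting, r from 0 to 0.7) agrees to within about half a percentage point in both columns.

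**3. Power if alpha is shared.** Holm's first step over five indices uses 0.05 / 5 = 0.01. With f = 0.14 and the formula in step 1:

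| Assumed rho | 52 per arm | 64 per arm |
|---|---|---|
| 0.3 | 42% | 53% |
| 0.5 | 59% | 71% |
| 0.7 | 85% | 93% |
| 0.8 | 97% | 99% |

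At rho = 0.5, the value that reproduces 104, a total of 154 would be needed for 80% power at 0.01. These figures are for an index tested at the first step; under Holm, later steps use larger levels, so they are a lower bound per index.

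**4. Power if all five must succeed.** Error is then controlled without adjustment, but joint power falls. With independent indices and the effect present on each, it is about 0.807⁵ = 34%.

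**The case against.** The strongest objection is that the document nowhere says an index is tested at 0.05, or that one significant index is enough. The level "specifying a significance level of *p* < 0.05" belongs to the power calculation, and results are promised as effect sizes with intervals. A multiplicity rule is also the kind of detail a condensed article leaves to a full protocol or analysis plan. This stands in part. The per-index rule is an inference, and the missing adjustment would not be a finding by itself. What remains is stated in the article: five variables are primary, and the trial is sized for one test. An unseen plan that splits alpha or requires all five departs from the stated power basis; one that picks a lead index departs from the definition of the primary outcome.

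Three stronger readings are tempting and are not supported.
- A reader might take 15% to 23% as the chance of a false success. Those rates count either direction, including Ubiquinol being worse, and hold only for r between 0 and 0.7. The hypothesis is improvement, for which the rates are about half.
- A reader might count ten tests, because the ANOVA examines a treatment effect and an interaction for each index, and reach 1 − 0.95¹⁰ = 40.1%. That needs a treatment main effect to count as success. The main effect averages baseline with Day 90, the primary question is change from baseline to Day 90, and only the interaction is powered. The text does not exclude that use, but does not state it either.
- A reader might conclude that one positive index could never be told from chance. The five indices are named in advance, so anyone can apply Holm to the published p-values, and a small enough p-value would survive.

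**Conclusion.** The point holds as a mismatch between a five-variable primary outcome and a one-test design. Read at 0.05 per index, which is inferred, the error rate is two to four and a half times nominal: 10.2% to 22.6% against 5% in either direction, and 5.1% to 11.9% against 2.5% in favour of Ubiquinol. The ranges rest on an assumed correlation among the indices from 0.9 down to 0. Inflation remains across this whole range; only its size depends on the assumption.

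The loss of power under an adjusted level depends heavily on rho, which the article does not state. The value 0.5 reproduces 52 per group but should not be credited to the plan. Should rho be near 0.7 or above, Holm would still leave per-index power above 80% at either sample size.

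**What to change.** In the Primary Outcome and Statistical Analysis sections, state that the Day-90 visit-by-treatment contrast is the only confirmatory effect for each index and that the treatment main effect is not a success criterion. Then choose one of two routes before unblinding.

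- **Keep five primaries.** Control familywise error at 5% across them with Holm, report adjusted p-values, and restate per-index power at the adjusted level with the assumed rho written down. The cost is less favourable stated power, as shown in step 3 of the working.
- **Name one index as sole primary** and make the other four secondary. Alpha stays at 0.05 and the present power basis stands. The cost is that the claim rests on one domain. The article's emphasis on memory does not settle the choice, since working memory capacity, episodic memory capacity and speed of retrieval could each be argued for, so the index must be named explicitly.

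Both routes are changes of wording and need no new data. The total of 128 and the 52 per group (2 × 52 = 104) must be reconciled in any case, because the restated power depends on which is meant.

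### The two-visit repeated-measures ANOVA is valid, but it amounts to a change-score test plus a diluted treatment main effect; adjusting for the baseline index score is more efficient, by an amount that depends on a correlation the protocol does not state

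*Protocol article*

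**What the plan says.** The Statistical Analysis section of the protocol article sets the primary model for the five CogTrack index scores: "Repeated measures analysis of variance (ANOVA) will be used to examine treatment and study visit × treatment interaction effects". It adds a subject-specific random intercept and specifies "treatment group as a between-group factor (CoQ_10_, placebo) and study visit as a repeated within-group factor (baseline, 90-days"). The baseline score is therefore one of the two outcome values, not a covariate.

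The covariates foreseen are demographic and depend on a preliminary test: "in the case of significant associations (*p* < 0.05), demographic variables will be included as covariates in the analysis". The baseline value of the index being analysed is not among them.

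The Participants section bases the sample size on the interaction alone, "with two treatment groups and two primary time points", and states that "there is an 80% chance of detecting a small-medium effect size (cohen’s *f* = 0.14) for the time × treatment group interaction". It gives no correlation between the two visits.

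**The concern.** Two features of the model work against the trial's own question, which is cognitive performance at 90 days.

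First, with only two visits the interaction compares mean change between arms. Change scores subtract the whole baseline value, although the best predictor of Day 90 uses only a fraction of it. Unless rho is close to 1, this adds noise that baseline adjustment would remove. It also leaves any chance baseline difference between the arms over-corrected in the estimate.

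Second, the treatment term in this model compares the arms on the average of the two visits. According to the Procedure section, capsules are handed out at the end of baseline testing, so half of that average cannot carry a treatment effect. The Statistical Analysis section names this term alongside the interaction and does not say which of the two decides.

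At stake are power that the collected data could supply, and a clear statement of which estimate answers the primary question.

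**Working it through.** **Inputs**
- Alpha 0.05 ("specifying a significance level of *p* < 0.05"), taken as two-sided because the interaction F test with 1 df is a two-sided t test. Power 80%, f = 0.14, two groups, two time points (Participants section).
- Sample size: "A total of 128 healthy elderly participants (52 per group) aged 60+ years will be randomized". Since 2 × 52 = 104, the total and the per-group figure disagree. That is a separate matter, so both N = 104 and N = 128 (64 per arm) are shown.
- rho: not stated, so an assumption; range shown.
- Dropout: not stated; none applied. Equal SD (sigma) at both visits. Baseline taken as pre-treatment, as the Procedure section describes.

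**Step 1: reproduce the plan's figure.** In the G*Power within-between interaction routine, lambda = N·m·f²/(1−rho) with m = 2 and df 1 and N−2. At N = 104 and rho = 0.5, lambda = 104 × 2 × 0.0196/0.5 = 8.15 and power = 80.7%. The smallest even N reaching 80% is 104. So rho = 0.5 reproduces 52 per group exactly, which makes it the implied value, though not a written one. At N = 128 and rho = 0.5 power is 88.2%; a power of exactly 80% there needs rho of about 0.37.

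**Step 2: the effect in SD units.** f = 0.14 corresponds to 4 × 0.14 = 0.56 SD between arms.

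**Step 3: interaction and change score.** On one simulated complete data set, the random-intercept model's interaction statistic and the change-score t were both 2.820. The identity holds for complete pairs.

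**Step 4: change score against baseline adjustment.** The change-score variance is 2(1−rho)sigma²; the ANCOVA residual variance is (1−rho²)sigma². Their ratio is (1−rho²)/[2(1−rho)] = (1+rho)/2. Lambda is therefore multiplied by 2/(1+rho), with df 1 and N−3. At N = 104 and rho = 0.5, lambda = 8.15 × 2/1.5 = 10.87 and power = 90.4%. A simulation of 20,000 trials gave 81.1% for the change score and 90.0% for ANCOVA. The N needed for 80% power falls from 104 to 78.

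Power with the 0.56 SD effect held fixed:

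| rho | Variance ratio | 52 per arm: change → adjusted | 64 per arm: change → adjusted |
|---|---|---|---|
| 0.3 | 0.65 | 66.7% → 84.2% | 75.7% → 90.9% |
| 0.5 | 0.75 | 80.7% → 90.4% | 88.2% → 95.3% |
| 0.6 | 0.80 | 88.5% → 94.2% | 94.0% → 97.6% |
| 0.7 | 0.85 | 95.5% → 97.7% | 98.2% → 99.3% |
| 0.8 | 0.90 | 99.4% → 99.7% | 99.9% → 99.9% or more |

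Alternatively, hold change-score power at 80.7% (lambda 8.15, 52 per arm) whatever rho is. Adjusted power is then 93.9% (rho 0.3), 90.4% (0.5), 88.5% (0.6), 86.6% (0.7), 84.6% (0.8) and 82.7% (0.9). For rho from 0.7 to 0.9 the gain is about 6 down to 2 points.

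**Step 5: the treatment main effect.** The average of the two visits differs between arms by 0.56/2 = 0.28 SD in expectation, with variance (1+rho)/2. At rho = 0.5 the standardised effect is 0.28/√0.75 = 0.323. Power is 37% with 52 per arm and 44% with 64 per arm. Under no treatment effect, 20,000 simulated trials gave a rejection rate of 5.05%, so the test keeps its size.

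**Step 6: chance imbalance.** With 52 per arm, one standard error of the baseline difference is √(2/52) = 0.196 SD. Given such a difference, the change-score estimate moves by (1−rho) × 0.196, about 0.10 SD at rho = 0.5, against a target of 0.56 SD. Averaged over randomisations this is zero.

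**The case against.** The strongest reply is that nothing here is wrong. The interaction test is unbiased under randomisation, it is the test that the sample size was built on, and it delivers the stated 80% under the implied correlation. The phrase about 90 days compared with baseline, read with the power statement, points to the interaction as the intended primary contrast. All of this stands. A reader might infer that the planned analysis is biased by regression to the mean, or that the trial falls short of its stated power because of it. The documents support neither: the cost is efficiency, and the shift from chance imbalance averages to zero.

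A reader might also take the treatment main effect to be invalid, or a declared route to success. It holds its nominal size, and no sentence makes it decisive. What remains is that it is named among the primary effects, is diluted by half, and is not ranked against the interaction.

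A third reply concerns size. A ten-point gain cannot be called the plan's own figure, because no rho is written down, and at rho of 0.7 or more with a fixed effect the gain is about two points or less. This also stands, and it is why the gain is given as a range.

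Finally, the planned random-intercept model can retain people who have only a baseline score, whereas a plain regression of Day 90 on baseline would drop them. This bears on the choice of remedy, not on the efficiency argument.

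**Conclusion.** The concern holds as a point of efficiency and clarity, not of validity. With complete pairs, equal variances and any rho below 1, baseline adjustment is more precise than the planned interaction by the factor (1+rho)/2, apart from one degree of freedom. At the implied rho of 0.5 this is worth about 10 points of power with 52 per arm and about 7 with 64. With the 0.56 SD effect fixed and 52 per arm, it ranges from about 17 points at rho 0.3 to about 2 at 0.7, and is negligible above that. The treatment main effect is a weak test of a half-sized quantity and should not serve as evidence of efficacy. The conclusion about the form of the analysis does not depend on rho; only the size of the gain does.

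**What to change.** In the Statistical Analysis section, name one primary contrast for each index: the treatment difference at Day 90 adjusted for the baseline score of that index, reported with its 95% CI. Preferably obtain it from a mixed model for both visits that constrains the arms to a common baseline mean and leaves the two-visit covariance unrestricted. This keeps participants without a Day-90 score and, for complete pairs, is in effect the same as ANCOVA of Day 90 on treatment and baseline. State that the treatment main effect of a baseline-inclusive model will not be used as a test of efficacy. Where the sample size is described, state the correlation that was assumed.

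The cost is wording and one degree of freedom. Baseline CogTrack is already part of the schedule, and neither sample size nor visits need to change.

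### Primary-analysis covariates are chosen by a significance test against the CogTrack scores instead of being named in advance, and as main effects they would add almost no precision to the powered visit × treatment test

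*Protocol article*

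**What the plan says.** The Statistical Analysis section of the protocol article describes the primary analysis as repeated-measures ANOVA by intention to treat, fitted "using a subject-specific random intercept term", with two visits (baseline and Day 90). The model "will be used to examine treatment and study visit × treatment interaction effects". It is applied to five index scores: "attentional intensity index, sustained attention index, working memory capacity index, episodic memory capacity index, and speed of retrieval index".

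On covariates, the section screens five demographics (age, sex, body weight, height and years or level of education) by Pearson correlation with the CogTrack scores. Wherever such a correlation is significant at the 5% level, the "demographic variables will be included as covariates in the analysis".

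The Participants section bases the sample size on the interaction: 80% power at Cohen's f = 0.14, two groups, two time points, significance level 0.05.

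The article does not say at which visit the correlations are computed, or whether selected covariates enter as main effects only or also crossed with visit. A fuller plan may settle those details, and their absence is not the point here. The selection rule itself is stated, and it is a choice about the primary analysis.

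**The concern.** A covariate set for a primary analysis is normally named before the data are seen, on the grounds that the variables predict the outcome. Here the set is the result of tests on the trial's own outcome scores. Two readers cannot know beforehand what the primary model for a given index will be, and the five indices may end up with five different models.

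There is also a question of purpose. Covariate adjustment is worth having because it sharpens the treatment contrast. In a two-visit model with a subject intercept, the powered contrast is a comparison of within-subject changes. A variable that does not change within a subject may have nothing to offer that contrast. The plan could then carry the drawback of data-driven selection without the usual benefit of adjustment.

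**Working it through.** **Inputs from the protocol article.** Five demographics, five indices, screening threshold 0.05, two visits, a random intercept, f = 0.14, power 80%, and a sample size given as 128 in total but also as 52 per group (104). Both sizes are carried below; that mismatch is a separate matter.

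**Assumptions (not in the article).** Correlation between visits ρ = 0.5, with a range where it matters; covariate–outcome correlation 0.4; interaction of 0.4 SD; 18.75% missing at Day 90, chosen as (128 − 104)/128.

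**1. The plan's own power figure.** For the within–between interaction, λ = f² × N × m/(1 − ρ), with m = 2 and df 1 and N − 2.
- N = 104: λ = 0.0196 × 104 × 2/0.5 = 8.15, power 80.7%.
- N = 128: λ = 0.0196 × 128 × 2/0.5 = 10.04, power 88.2%.

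The stated 80% is reproduced for 52 per group at ρ = 0.5. It confirms that the powered test is the interaction.

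**2. How easily the screen selects.** The critical correlation is r = t/√(n − 2 + t²): 0.193 at n = 104 and 0.174 at n = 128. If none of the demographics were associated with the scores:
- expected selections over all indices: 5 × 5 × 0.05 = 1.25;
- chance of at least one selection for a given index: 1 − 0.95⁵ = 22.6%;
- chance of at least one over 25 tests, if independent: 1 − 0.95²⁵ = 72.3%.

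**3. What a main-effect covariate does to the interaction.** For subject i with treatment t and covariate x:
- baseline: y₀ = a + bt + γx + u + e₀
- Day 90: y₁ = a + d + (b + δ)t + γx + u + e₁
- change: y₁ − y₀ = d + δt + (e₁ − e₀)

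The term γx cancels, so with complete data the estimate and standard error of δ are the same with or without x. If x is crossed with visit (coefficient κ at Day 90), κx remains in the change and the test of δ does depend on x.

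**4. Simulation check.** REML random-intercept fits, 1000 trials per scenario, N = 128, each compared with the model without the covariate. SE ratios are for the interaction term.

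| Scenario | How covariate enters | Mean SE ratio (range) | Decisions changed per 1000 |
|---|---|---|---|
| Complete data | main effect | 1.000 (1.000–1.000) | 0 |
| 18.75% missing, at random | main effect | 0.996 (0.973–1.017) | 19 |
| 18.75% missing, depending on covariate | main effect | 0.993 (0.965–1.014) | 36 |
| Complete, covariate effect same at both visits | crossed with visit | 1.004 (0.961–1.046) | 18 |
| Complete, covariate effect differs by 0.3 between visits | crossed with visit | 0.962 (0.861–1.067) | 90 |

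The covariate in these runs was fixed, not selected. The last column therefore shows how sensitive the decision is to adjustment. It is not an error rate of the screening rule.

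**5. Where a main effect does help.** The standard error of the treatment term fell to about 0.92 of its unadjusted value with complete data. With baseline as the reference visit that term is the group difference before treatment; with centred coding it averages the two visits. Neither is the change from baseline to Day 90.

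**6. What a Day-90 model would give.** With equal variances σ², the change score has variance 2σ²(1 − ρ), and the Day-90 score adjusted for baseline has σ²(1 − ρ²). The ratio is (1 + ρ)/2: 0.65 at ρ = 0.3, 0.75 at ρ = 0.5, 0.90 at ρ = 0.8. Any further gain from age, education and sex is not counted.

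**The case against.** The rule names its candidates and its threshold in advance and does not use treatment assignment, so it is an algorithm and not open discretion. The correlations may be computed on baseline scores, before any treatment. A chance selection costs about one degree of freedom, and 1.25 such selections assumes that nothing is associated, although the Aims section itself expects age to matter. If main-effect covariates leave the powered test alone, selecting them cannot bias that test either. A Day-90 model also goes beyond what is needed to repair the screen.

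Much of this stands. Two stronger readings should be set aside.
- A reader might infer that the covariates cannot alter the interaction test at all. That is exact only for main effects with complete two-visit data. The analysis is by intention to treat, so participants with a baseline score only may contribute, and the text does not exclude covariate × visit terms. Both change the test.
- A reader might infer that the rule inflates the false-positive rate. Nothing in the documents or in the calculations shows that.

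What the objection does not do is give the screen a useful role. As main effects the selected covariates are nearly idle for the powered test; crossed with visit, an outcome-based choice feeds into it.

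**Conclusion.** The point holds in limited form. The article fixes a selection rule that leaves the primary model undetermined until the scores are seen and allows it to differ between indices. Under the main-effect reading, which is an assumption, the adjustment adds nothing to the powered test with complete data and on average less than 1% in standard error at about 19% dropout. Under the crossed reading, adjustment can change the conclusion in roughly 2% to 9% of simulated trials, so the choice of covariates then matters to the primary result.

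The case for change rests on having a model that is known in advance and on a cheap gain in precision; no demonstrated error in the test is claimed. The percentages depend on the assumed ρ, covariate correlation, effect and dropout. The cancellation in the complete-data case does not.

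**What to change.** Remove the correlation screen as a selection rule and keep the correlations as descriptive output. For each of the five indices, prespecify a model for the Day-90 score with treatment, the baseline score of that index, age, education and sex, included whatever their significance. State the handling of missing Day-90 scores with it, because participants without one add nothing to such a regression on their own.

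If the repeated-measures model is preferred, the minimum repair is to name the same covariates for every index and state that they are crossed with visit. That removes the selection but does not bring the (1 + ρ)/2 gain.

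The cost is a change of wording and about 4 residual degrees of freedom, out of 102 at N = 104 or 126 at N = 128. The Procedure section already collects the three demographics at screening, and CogTrack is taken at baseline. Because (1 + ρ)/2 is below 1 for any ρ below 1, the change should not weaken the power statement under equal variances, apart from those few degrees of freedom.
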